### Data collection, monitoring, management and reporting

Data collection is purpose designed and will be facilitated by a highly secured and password protected online software application. Study protocols, templates for assessing CKD risk, links to the QKidney risk calculator, template for GP referral, QKidney health advice, template for QUM service will be included in the software along with specific guides to support access and familiarisation. Intervention group pharmacies will also be able to record the POCT results in the software. This will maximise trial efficiency and reduce the burden on pharmacists.

Adherence to the study protocol will be regularly monitored for accuracy and completeness by the project manager and research officers using the online study website and site visits. In addition, project officers will use a range of communication strategies to ensure that the community pharmacists are kept informed of the latest developments of the study, and to provide ongoing support to the pharmacists and these include regular phone calls and bulk emailing options to allow an early action where pharmacies require additional support with the study.

Data collection including pre-screening, screening and post-screening activities and the respective time points are outlined in table 1. The study is set to take place over 2 years (March 2023 to May 2025), and will include enrolling pharmacists and patients, 6-month and 12-month follow-ups and report writing.

**Table 1 T1:** Study procedures and time points

Procedure	Baseline	6 weeks	3 months	6 months	12 months
Pre-screening/screening activities					
Site randomisation	X				
Information sheet	X				
Pharmacist/participant consent	X				
Initial screening	X				
Pharmacy survey (current services)	X				
Inclusion/exclusion criteria - review	X				
Demography and medical history	X				
Outcome assessment					
Proportion of people with CKD				X	X
Changes in # of PIMs				X	X
% of participants with CKD risk factors	X			X	X
QKidney risk profiles	X				
% Participants referred to GP	X				
% Participants taking up referral with GP				X	X
Phone/SMS reminder (PO/RA)		X			
Other outcomes (health-related quality of life, well-being)	X				X
Study evaluations					
Economic evaluation (health resource use and costs)					X
Pharmacist midtrial Interview			X		X
Pharmacist end of trial interview					X
GP satisfaction					X
Participant knowledge/satisfaction survey					X
Study compliance audit	X		X	X	X

CKD, chronic kidney disease; GP, general practitioner; PIMs, Potentially Inappropriate Medications; PO, Project Officer(s); SMS, short messaging service.

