**Figure 1 F1:**
[figure not shown]
Procedures of recruitment of participants. BP, blood pressure; CKD, chronic kidney disease; CrCL, creatinine clearance; eGFR; estimated glomerular filtration rate; GP, general practitioner; NSW, New South Wales; POCT, Point-of-Care Testing; PSA, Pharmaceutical Society of Australia; QUM, quality use of medicines; SCr, serum creatinine; SMS, short messaging service; VIC, Victoria.

Screening participants will be recruited through the targeted community pharmacies. The recruitment process involves the pharmacists discussing the study and confirming participant eligibility. The pharmacist will manage potential participants using a purpose-built online software application hosted on a cloud-based server at The University of Sydney. This will ensure the integration of the recruitment process, including the delivery of intervention into the pharmacy recording platform and thereby automate key processes, such as risk assessment, medication history taking, referral letter production and follow-up. Also, direct storage of data in the cloud server will ensure no data are lost due to any systemic issues arising from individual pharmacies.

Following identification of screening participants, those who are eligible and willing to participate will be provided with the participant information statement to read and be asked to sign two consent forms. The first one is to participate in the study and to access their medical records from the GP and My Health Record (a secure online platform used in Australia used to store key healthcare information—this will facilitate pharmacists’ verification of clinical information when they make referral to GPs). The second consent will be used to release their Medicare Benefits Schedule (MBS) and PBS claims data from Services Australia.

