### Data analysis plan

All data will be reported following the Consolidated Standards of Reporting Trial guidelines.^42^ Baseline clinical and demographic characteristics will be summarised using frequencies and percentages for categorical variables, and means, SD, medians, IQRs and minimum and maximum values for continuous variables, as appropriate. All statistical analyses for the primary and secondary outcomes will follow the intention-to-treat (ITT) principle. The ITT population will include all randomised participants based on their initial assignment to either intervention or control group and include any participants who prematurely withdraw or poorly comply with the protocol.

All primary and secondary analyses will use Generalised Estimating Equations with pharmacy as the unit of clustering, using the model appropriate for the distribution of the outcome. The analysis of the primary outcome (reported as a binary variable 0=not diagnosed with CKD, 1=diagnosed with CKD) will use a logistic regression within a model to test the effectiveness of the intervention. Analysis will first be unadjusted (including as fixed factors group membership and the stratification variable, region), followed by analysis adjusted for relevant baseline covariates (age, gender, blood pressure measures, BMI, socioeconomic status and location of pharmacies), as well as the fixed factors from the unadjusted analysis. Binary secondary outcomes such as percentage of participants with CKD risk factors, those having a GP review, and those with potentially inappropriate medications will be analysed using a similar approach as that for the primary outcome.

Additional outcomes including numbers of recommendations made by pharmacists, numbers of medication-related hospitalisations or acceptance rates by GPs will be analysed using negative binomial regression (or Poisson regression, depending on distribution of the outcome) or logistic regression and will include unadjusted and adjusted analyses as per the primary outcome.

For humanistic outcomes such as participant’s health-related quality of life, as well as outcomes on GP satisfaction and participant knowledge/satisfaction, we will use linear regression. All analyses will be presented using unadjusted and adjusted models as per the primary outcome. For the proportion of participants screened in the trial (process indicator), we will use the Mantel-Haenszel extension of a χ^2^ Test of Independence.

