### Economic evaluation

Health service utilisation will be measured through Medicare and Pharmaceutical Benefits Schemes (MBS and PBS) data linkage, to quantify the symptom-specific and total health service resource use and costs at 12 months, by allocated group. The Consolidated Health Economic Evaluation Reporting Standards guidelines (online supplemental appendix 3) will be followed when reporting the health economic evaluation.^44^

10.1136/bmjopen-2023-079110.supp3Supplementary data

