### Costs

Cost-effectiveness of the intervention will be calculated from a health service provider perspective considering costs incurred by the pharmacists and the government (PBS/MBS) but will not include costs borne by screening participants (eg, through co-payments charged by GPs). Healthcare resource use including GP visits, specialist visits, diagnostic tests, medicine, hospitalisation, emergency admissions will be collected from MBS/PBS history, medication prescription and dispensing records and previous hospital discharge summaries from My Health Record. Unit costs will be collected based on MBS/PBS item numbers, Australian Refined Diagnosis Related Groups and Triage codes. Measured costs will include pharmacist time to facilitate data collection at each pharmacy.

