#### Costs analysis

The cost per new CKD case diagnosis for each group will be estimated and compared. We will assess whether the average cost of the new CKD case diagnosis in the intervention group is lower or higher than the average cost of the new CKD case diagnosis in the control group. We hypothesise that there is likely to be a difference in average costs per new CKD case diagnosis across the sites in the same cluster and across the clusters from the metropolitan and rural settings. This is due to the differences in sample size, local unit prices of equipment, staff costs and different established local practices.

Differences in overall mean costs between the two groups will be analysed using Generalised Linear Mixed Model. The distribution of residuals from the regression model will be examined and a decision will be made as to whether the costs should be logarithm transformed. Any extreme costs will be carefully examined to decide if they should be considered as extreme outliers and should be trimmed (removed) from the analysis. It is anticipated there will be some missing data. Missing costs data will be examined to ascertain whether it is missing completely at random, missing at random or missing not at random. Simple and multiple imputation methods will be considered based on the pattern of missingness.^45^

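### Costs are scheduled at 12 months only and no pre-enrolment cost enters the named model or covariates; stating a claims look-back and adjusting for prior cost would be a cheap gain

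*Protocol article*

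**What the plan says.** All references are to the protocol article.

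- **Schedule.** Table 1 (Data collection, monitoring, management and reporting) has one mark for "Economic evaluation (health resource use and costs", under 12 months. The row "Other outcomes (health-related quality of life, well-being" is marked at baseline and at 12 months.
- **Window.** Economic evaluation uses linked claims "to quantify the symptom-specific and total health service resource use and costs at 12 months, by allocated group".
- **Sources.** Under Costs, resource use "will be collected from MBS/PBS history, medication prescription and dispensing records and previous hospital discharge summaries from My Health Record". No look-back period is given.
- **Model.** Costs analysis states: "Differences in overall mean costs between the two groups will be analysed using Generalised Linear Mixed Model". It goes on to log transformation, trimming and missing data, but lists no covariates.
- **General adjustment set.** The Data analysis plan names "age, gender, blood pressure measures, BMI, socioeconomic status and location of pharmacies". Prior use or cost is not among them.
- **Consent.** Clinical protocol and recruitment procedure: "The second consent will be used to release their Medicare Benefits Schedule (MBS) and PBS claims data from Services Australia". The period is not stated.

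**The concern.** Quality of life has a baseline value in the schedule and cost has none. The cost difference is the numerator of the incremental ratio, so noise or imbalance in it reaches the economic conclusion directly.

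Imbalance in prior health-care use is plausible in this design. Clusters are allocated first, and pharmacists in the allocated pharmacies then discuss the study and confirm eligibility. They know their arm, because the training modules differ and only intervention pharmacists are trained on the testing device. The offer differs too. People with known CKD receive advice and a factsheet in the control arm, but a medication review in the intervention arm, with a kidney function test if none is recent. Matching on location and socioeconomic status balances areas, not who is enrolled within a pharmacy. The baseline survey meant to inform comparability and the economic analysis describes pharmacies, not participants.

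The choice of covariates can wait for an analysis plan. The claims window is less safe to leave, because a later plan cannot adjust for claims that were never requested or consented to.

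**Working it through.** **The plan's own figure.** There is no sample size, standard deviation (SD) or intracluster correlation (ICC) for cost. The stated size concerns diagnosis, and it reproduces: 10% v 15%, two-sided alpha 0.05 and 80% power need 686 per arm. The design effect is 1 + 29 × 0.05 = 2.45. Then 686 × 2.45 = 1,680.7, and 1,680.7 / 30 = 56.02, so 57 clusters per arm. With 61 per arm, 2 × 61 × 30 = 3,660 participants, or 1,830 per arm.

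**Assumed inputs (none is in the documents).** Correlation r between prior-year and trial-year cost: 0.3, 0.5, 0.7, taken as equal within and between clusters. Cost ICC: 0.05, with 0.01 and 0.10 as alternatives. Prior-cost imbalance between arms: d = 0.1 SD. Equal spread in both years.

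**Precision.** In SD units the unadjusted standard error is SE = √(2 × 2.45 / 1,830) = 0.052, a 95% half-width of 0.101. A prior-cost covariate multiplies the variance by 1 − r² and the interval width by √(1 − r²). The equivalent unadjusted sample is 3,660 / (1 − r²).

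| r | Variance cut (r²) | Adjusted SE | Interval narrower by | Equivalent sample |
|---|---|---|---|---|
| 0.3 | 9% | 0.049 | 5% | 4,022 (+10%) |
| 0.5 | 25% | 0.045 | 13% | 4,880 (+33%) |
| 0.7 | 49% | 0.037 | 29% | 7,176 (+96%) |

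**Imbalance.** The unadjusted difference is shifted by r × d. With d = 0.1 SD and cost ICC 0.05:

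| r | Shift (SD) | Shift / SE | Two-sided false-positive rate |
|---|---|---|---|
| 0.3 | 0.03 | 0.6 | 9% |
| 0.5 | 0.05 | 1.0 | 16% |
| 0.7 | 0.07 | 1.4 | 27% |

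The nominal rate is 5%. For cost ICC from 0.01 to 0.10 the unadjusted SE runs from 0.038 to 0.065, and the shift from about 0.5 to 1.9 SE. These rows apply to imbalance left over after matching and any other covariates.

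**Limit on the upper figures.** The Costs section prices hospital and emergency care through diagnosis-group and triage codes, uses discharge summaries, and adds pharmacist time. Prior Medicare and pharmaceutical claims would cover only part of that outcome, so r = 0.7 is optimistic. The formula is also for a linear model, while the plan allows log transformation and trimming.

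**The case against.** The strongest reply is that the article is silent rather than wrong. Costs analysis names a model class and no covariates, so a prior-cost term is not excluded and may sit in an analysis plan that is not shown. This stands: a reader might infer that the plan rules out baseline adjustment of costs, and the text does not support that.

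A reader might also infer from Table 1 that no earlier claims will be obtained. The row sits under study evaluations, and the 12-month mark may simply be when linkage is done. The Costs section speaks of claims history and previous discharge summaries, and the consent form is not shown, so the request may already reach back. This stands as well, but no pre-enrolment window or baseline use of such data is stated anywhere.

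Third, the comparison need not be raw. Clusters are matched on location and socioeconomic status. The Data analysis plan promises adjusted models for all primary and secondary analyses, and cost effectiveness is a secondary outcome. Whether that list carries over is unclear, since that section uses generalised estimating equations and the cost section a mixed model. Part of any imbalance may therefore be absorbed, but neither route includes prior use.

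Finally, every magnitude is assumed and neither primary outcome is touched. That is correct and limits the weight of the point.

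**Conclusion.** The point holds as a worthwhile, inexpensive improvement to a secondary outcome, not as an error that invalidates the economic analysis. As written, costs have no stated pre-enrolment measurement, and neither the cost model nor the listed covariates include prior use or cost. The cost difference is therefore less precise than it could be, and exposed to imbalance in prior use that matching and the listed covariates do not capture.

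For an assumed correlation of 0.3 to 0.7, adjustment would cut residual variance by 9% to 49%, with the upper end optimistic for a claims-only covariate. The shift from imbalance depends on an assumed size of imbalance as well. The documents do not support saying that the estimate will be imprecise in absolute terms, or that it will carry every recruitment imbalance: they give no cost SD, ICC or correlation, and show no actual imbalance.

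**What to change.** 1. In Clinical protocol and recruitment procedure and in Economic evaluation, state that the claims request covers 12 months before to 12 months after each participant's enrolment, and check that the consent wording covers the earlier year.
2. In Costs analysis, add prior-year Medicare and pharmaceutical claims cost as a covariate in the mixed model.
3. Report prior-year claims cost by arm as a baseline characteristic, and mark resource use at baseline in Table 1.

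The price is a longer date range in the data request, possibly one line in the consent form, and one model term. Prior cost will be missing for participants who do not consent to claims release, whose claims-based follow-up costs are missing already. No visit is added.

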### Outcomes

#### Primary outcome measures

Proportion of patients newly diagnosed with CKD at the end of the study period.Changes in the number of medications considered problematic in kidney disease (number of medications prescribed at inappropriately high dose, number of contraindicated medications or detrimental drug interactions).

#### Secondary outcome measures

Proportion of screening participants with inappropriate medications (number of medications at inappropriate high dose based on the kidney function and number of contraindicated medications).Proportion of eligible participants without potentially beneficial medications (eg, renin angiotensin system inhibitors or sodium glucose co-transporter 2 inhibitors).The number and characteristics of proposed medication adjustments recommended by pharmacists and acceptance rates by GPs.Proportion of participants with CKD risk factors.Proportion of participants screened (process indicator).Participants’ QKidney risk profiles.Percentage of participants referred to their GP.Percentage of participants who take up referral with their GP.Number of hospitalisations due to medication-related events.Cost effectiveness.Health-related quality of life, consumer well-being and satisfaction.

Both the intervention and control group participants will be followed-up by the project officers/pharmacists at 6 and 12 months to determine if they have had any additional blood tests, and changes to their medications, and hospitalisations.

Primary outcomes will be determined based on data collected from GPs. Health-related quality of life and overall participant well-being will be measured using the EuroQoL-5D-5L, which consists of a descriptive system and a Visual Analogue Scale.^39^ The EQ-5D-5L is scored on a 0–1 utility scale, where 0=death and 1=full and complete health. Unit values will be informed by Australian population estimates.^40^ A minimally important difference of 0.07 (7%) change in utility on the EQ-5D-5L scale is considered to be clinically meaningful.^41^

Screening participants’ satisfaction with the service and willingness to pay for the service will be determined by a telephone questionnaire, which will include items relating to service approval (5-point Likert scale); and open-ended questions to elicit reasons for approval and satisfaction ratings. Screening participants’ willingness to pay for the service will also be determined including the maximum amount. Satisfaction of pharmacists (at midtrial and end of trial) with the screening and QUM services will be assessed using electronic surveys. The GPs involved in the care of the participants will also be sent a survey at the end of the trial to determine their satisfaction and any effects on their practice.

A purposive sample of screening participants and GPs will be invited for a follow-up interview based on their responses to the surveys. The aim will be to identify issues that may limit the effectiveness of the proposed intervention. Pharmacist satisfaction with the service will be determined by inviting pharmacists who delivered the intervention to attend focus group discussions. The topics covered will include overall pharmacist experience of the screening programme, including consumer perspectives, GP communications, business impact and implications for future implementation.

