### Hypotheses

We hypothesise that the use of a POCT with CKD risk assessment (POCT+QKidney Risk Assessment: Intervention Group) in community pharmacies will result in (1) a significantly improved detection of previously unknown CKD cases, and (2) reduced use of potentially inappropriate medications when compared with CKD risk assessment alone (QKidney Risk Assessment: Control Group).

Other hypotheses related to the primary hypothesis are that the Intervention Group will be associated with a statistically significant increase in the proportions of those who are referred to the GP, take up referral with the GP, are newly diagnosed with CKD compared with the Control Group.

Additionally, the incorporation of POCT in conjunction with the QKidney Risk Assessment will lead to enhanced utilisation of kidney beneficial medications (ie, those that slow kidney disease progression), a long-term economic benefit and improved humanistic outcomes.

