Following recruitment, screening participants in the ***control*** group, if they are known patients with CKD (stages 1–4; based on self-report), will be provided with lifestyle advice and counselling on medications to avoid in kidney disease along with a Kidney Health Australia factsheet on ‘Looking after yourself with kidney disease’. All other control group patients will have their risk of developing CKD computed using the QKidney risk calculator,^38^ or based on blood pressure levels, if they have at least one of the known CKD risk factors. Participants will be advised of an appropriate action based on their calculated risk. All participants will be provided with lifestyle advice using a range of educational fact sheets, sourced from Kidney Health Australia resources, targeting their risk factors for CKD.

Following recruitment, participants in the ***intervention*** group will be divided into two groups.

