Those with pre-existing CKD (Stages 1–4; based on self-report) and a serum creatinine (SCr) and eGFR measured within the last 3 months (accessed via My Health Record) will have their dispensing history and medication event summaries (My Health Record) reviewed to determine the presence of any medications considered problematic in kidney disease. Participants with inappropriate medication, doses or medication combinations based on their kidney function will have recommendations to adjust the doses of medications or cease contraindicated medications (QUM service) to their GP. Additionally, participants who, because of their kidney function, are eligible but not receiving potentially beneficial medications (eg, renin angiotensin system inhibitors or sodium glucose co-transporter 2 inhibitors) will have recommendations provided to their GPs to consider starting these medications. The pharmacists will be encouraged to upload their recommendations on the My Health Record platform as event summaries. Participants with no SCr/eGFR recorded in the last 3 months will have their kidney function determined using POCT followed by the QUM service.Participants with no prior history of CKD and at least one CKD risk factor will have their risk of developing CKD computed using the QKidney risk calculator. Participants who return with a moderate to high risk (>3% of developing moderate to severe CKD over 5 years) will have their kidney function determined using a POCT device for SCr and eGFR and will have their dispensing history reviewed to determine the presence of any medications considered problematic in kidney disease. Participants with any inappropriate dosages or contraindicated medications as per their kidney function will have recommendations to their GP to adjust the doses of medications/ceasing contraindicated medications or medication interactions (QUM service). Also, the recommendations may include introduction of potentially beneficial medications as highlighted above. The pharmacists will be encouraged to upload their recommendations on My Health Record as event summaries.

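### The outcome on kidney-beneficial medicines uses a denominator (participants eligible by kidney function) that the trial itself ascertains only in the intervention arm, so the arms are not compared on like groups

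*Protocol article*

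**What the plan says.** The Hypotheses section expects that adding point-of-care testing (POCT) to the QKidney assessment "will lead to enhanced utilisation of kidney beneficial medications". Among the secondary outcome measures, the only one on use of these medicines is "Proportion of eligible participants without potentially beneficial medications".

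Eligibility is explained only under Clinical protocol and recruitment procedure, in the intervention-arm service, which refers to "participants who, because of their kidney function, are eligible but not receiving potentially beneficial medications". Kidney function is obtained differently in the two arms:

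- **Intervention, no prior CKD, moderate to high risk:** they "will have their kidney function determined using a POCT device for SCr and eGFR".
- **Intervention, known CKD:** a result from the last 3 months is used. Otherwise, "Participants with no SCr/eGFR recorded in the last 3 months will have their kidney function determined using POCT".
- **Control, known CKD:** advice, counselling and a factsheet, with no test.
- **Control, others:** "All other control group patients will have their risk of developing CKD computed using the QKidney risk calculator", or an assessment based on blood pressure, with no test.

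Both arms consent to access to GP records and My Health Record, and both are followed up at 6 and 12 months "to determine if they have had any additional blood tests, and changes to their medications, and hospitalisations". The Data analysis plan says that all primary and secondary analyses follow intention to treat, with everyone randomised kept in the assigned group.

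**The concern.** Belonging to the eligible group requires a kidney function result. The intervention supplies that result to people who would otherwise lack one; the control condition does not. Finding previously unknown CKD is the trial's first aim, so the better the intervention works, the further the two denominators drift apart. A person with unknown low kidney function enters the intervention denominator, while the matching control participant is left out unless usual care happens to test them.

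If people found only by POCT are less often treated already, they raise the untreated share in the intervention arm before any prescribing changes. The result would then mix a change in prescribing with a change in who is counted. It matters because no other listed outcome addresses this hypothesis.

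**Working it through.** The plan gives no figure for this outcome, so there is none to reproduce. Two document figures serve as rough guides to control ascertainment, both from the Background: 53% of moderate- or high-risk pilot participants later had a kidney function test, and 20% of patients meeting CKD criteria had a documented diagnosis. All treatment and uptake rates below are assumptions.

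**Calculation A.** Of all truly eligible people, 20% are documented, of whom 70% are treated; of the rest, 20% are treated. A share r is ascertained by 12 months. In the intervention arm r = 0.75, and 20% of untreated newly ascertained people start treatment.

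- Control untreated share, no new starts: 1 − [0.20×0.7 + (r − 0.20)×0.2]/r = 0.8 − 0.1/r.
- Untreated share with 20% starts: 1 − [0.20×0.7 + (r − 0.20)×(0.2 + 0.2×0.8)]/r = 0.64 − 0.068/r.
- Intervention as worded: 0.64 − 0.068/0.75 = 54.9%.
- True untreated share among all eligible, no new starts: 1 − (0.20×0.7 + 0.80×0.2) = 70.0%.
- True untreated share in the intervention arm: 70.0% − 0.55×0.8×0.2 = 61.2%.

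| Control r | New starts in control | Control v intervention, as worded | Difference as worded | True difference |
|---|---|---|---|---|
| 25% | none | 40.0% v 54.9% | +14.9 | −8.8 |
| 40% | none | 55.0% v 54.9% | −0.1 | −8.8 |
| 53% | none | 61.1% v 54.9% | −6.2 | −8.8 |
| 62.4% | none | 64.0% v 54.9% | −9.0 | −8.8 |
| 53% | 20% | 51.2% v 54.9% | +3.8 | −3.5 |

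Differences are in percentage points; negative favours the intervention. The 62.4% row applies the pilot's 53% only to the undocumented 80%: 0.20 + 0.80×0.53. In the last row the true difference is −(0.55 − 0.33)×0.8×0.2 = −3.5. Without control starts, the sign reverses when 0.8 − 0.1/r < 0.549, that is, below about r = 40%.

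**Calculation B.** This uses a different structure. Let a be the untreated share among those known anyway, b the untreated share among those found only by POCT, w the share of the intervention denominator that POCT adds, and u the fraction of untreated intervention participants who start. POCT is taken to find everyone eligible, so w = 1 − control ascertainment.

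- Control as worded: a. Intervention as worded: (1 − u)[(1 − w)a + wb].
- The sign reverses when u < 1 − a/[(1 − w)a + wb].

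Take a = 40% and b = 70%.

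- **Ascertainment 53%:** the bracket is 0.53×0.4 + 0.47×0.7 = 0.541. With u = 20% the outcome is 40.0% v 43.3% (+3.3 points), against a true 54.1% v 43.3% (−10.8). The reversal threshold is u = 26.1%. With u = 40% it shows −7.5 against a true −21.6.
- **Ascertainment 20%:** the bracket is 0.20×0.4 + 0.80×0.7 = 0.640. With u = 20% the outcome is 40.0% v 51.2% (+11.2), against a true 64.0% v 51.2% (−12.8). The threshold is u = 37.5%. With u = 40% it shows −1.6 against a true −25.6.
- **If b = a:** the bracket equals a, and the distortion disappears.

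A grid on the same structure (control ascertainment 25% or 50%; intervention 60%, 80% or 100%; a = 30% or 40%; b = 70%; u = 20% or 40%) reverses the sign in 13 of 24 settings.

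**The case against.** The strongest reply has four parts.

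**The denominator is not defined by the test.** The outcome speaks only of eligible participants. The kidney-function wording comes from a rule on when an intervention pharmacist makes a recommendation, and an operational definition can be left to the full protocol or SAP. This stands in part. But any later definition based on kidney function meets the same obstacle, since the trial produces no result for untested controls.

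**Control results exist.** Record access and the follow-up questions on blood tests can identify eligible controls who have no CKD diagnosis. This stands, and it makes the 20% documentation figure a poor proxy: those patients met CKD criteria without the diagnosis being documented. The pilot's 53% is the closer analogue. It still leaves the arms unequal.

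**Apparent harm is not established.** A reader might infer that a real benefit will be reported as harm, as in the 40.0% v 54.9% row. The documents do not support that. The row rests on 25% control ascertainment and on assumed treatment rates. With 53% and no control starts the sign is right, and at 62.4% the error is negligible.

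**The quantity is not foreign to the hypothesis.** A reader might also infer that the outcome answers a different question. It does not: the untreated share among eligible people is the complement of use among them, which is a fair reading of "enhanced utilisation of kidney beneficial medications". The fault lies in unequal ascertainment.

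**Conclusion.** The point holds as one of unequal ascertainment. A denominator resting on kidney function, measured by the trial in one arm only, is partly a result of the intervention and does not give the promised intention-to-treat comparison. Equal record access does not repair this, because records cannot contain tests that were never done.

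The bias runs against the intervention if people found only by POCT are untreated more often than those already known. This is plausible, but the article gives no data on it. Most of the settings worked above understate the benefit or reverse its sign; one shows almost no error. Reversal depends on low control ascertainment, low uptake, or newly ascertained controls also starting treatment. No single figure should be quoted as the expected bias.

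This is a secondary outcome, so the trial's main conclusions are not at risk. The change should still be made, since the hypothesis has no other listed measure.

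**What to change.** Make the between-arm comparison on a denominator that does not depend on POCT. Either:

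- use the proportion of all enrolled participants dispensed a listed kidney-beneficial medicine at 12 months, from PBS claims, adjusted for baseline use where a look-back in the same claims is available; or
- use a subgroup fixed from baseline characteristics recorded alike in both arms before POCT.

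Report eligible but untreated participants as a description within the intervention arm only.

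Participants in both arms are asked to consent to release of PBS claims, and the Economic evaluation section already plans linkage by allocated group at 12 months. The work is therefore a change of outcome wording and an analysis of data already requested. Whether the request covers a period before enrolment needs to be confirmed. The price is a smaller absolute difference, because the all-participant denominator includes people for whom these medicines may not be relevant. The baseline-defined subgroup may dilute less, but it replaces kidney function with a proxy that would have to be justified.
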